After the psychological needs training, participants will be asked to choose one psychological need that they wish to focus on during the four-week intervention period. While they are free to choose whichever of the six needs they want to work with, we recommend aiming to work with the psychological need that they scored the lowest on. This recommendation is made to support more balanced needs satisfaction across different needs, which has been found to be associated with higher reported well-being [32]. Participants will work in small groups and will be assisted by trainers to come up with their individual SMART off-job crafting goals. In the end, they will write their goals down in their personal booklets. As forming implementation intentions has been shown to improve goal achievement [33], participants will write a postcard for themselves where they outline how implementing their chosen DRAMMA goal will benefit them, what might potentially interfere with achieving the goal and how to overcome these barriers. The postcards will be sent to the participants during the second week of the four-week intervention as a positive reminder to continue working on their goals.

Next, participants will follow an app tutorial outlining the main functions of the smartphone app Everydaily and create their personal off-job crafting projects in the app. At the end of the first training session, trainers will summarize the main points of the training and the next steps, and participants will have a chance to ask questions about both this training session and the intervention in general.

After the four-week intervention period, participants will attend a second half-day training session. During this session, they first fill out the last weekly questionnaire and will receive new individual needs satisfaction scores, which they can compare to their baseline scores. Next, they have a chance to reflect on their experiences by identifying enablers and barriers that affected their off-job crafting during the intervention period. They will then review their previous goals, set future goals, and have the chance to ask questions. Additionally, we will ask participants to fill out a process evaluation questionnaire at the end of the training session to gather information about intervention reach, dose received and participants’ attitudes toward the intervention [34].

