#### Process evaluation

At the end of the second training session, a process evaluation will be conducted to provide insights into the process of the intervention and the mechanisms that might have influenced the effectiveness of the intervention. Participants are asked to indicate the extent that they participated in the intervention, the level of effort invested in following the intervention, and whether they perceived participation in the intervention to be time-consuming. Additionally, we ask them to report their level on enjoyment and satisfaction with the intervention, relevance of the training content, and the type of perceived support that they received from others during the intervention. We also ask participants to assess whether they gained new skills and knowledge from the intervention, and to express their level of satisfaction with the performance of the trainers during on-site trainings. Regarding the smartphone app Everydaily, we ask participants to indicate how many Dailys they have completed and whether they also logged all the completed Dailys to the app to gain better understanding about participants’ app use. Regarding off-job crafting goal setting, participants are asked to indicate the psychological need that they worked on during the intervention period and write down the goal that they set during the first training session. They are then asked to rate their goal attainment during the intervention period on a scale from 0 to 100%. Finally, participants can describe the most important things that they learned during the intervention and provide any additional comments.

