### Strengths and limitations

The main limitation of the study is that the intervention includes several on- and offline components. With the two-armed randomized control trial (intervention versus waitlist control), it is not possible to evaluate each specific component separately, and it is therefore difficult to establish which intervention components are the most effective. However, we aim to conduct a thorough process evaluation to gain insights into recruitment, reach, fidelity, participants’ attitudes toward the intervention, context, implementation, dose delivered and dose received, and to link the effect and process evaluation results to better understand the different mechanisms that might have influenced the effectiveness of the intervention [34]. Secondly, as the intervention and the waitlist control group participants are recruited from the same organization and potentially form the same departments, contamination may occur. While the trainings, booklets and smartphone app are first only made available for the intervention group, there is still a chance that colleagues participating in the intervention could share their training materials with the waitlist control group participants. To minimize this risk, intervention participants are specifically reminded not to share the training materials with the control group members until the end of the intervention period. Thirdly, another limitation might be participants’ non-adherence to the instructions or dropping out of the study entirely. In order to avoid these potential complications, we will explain the procedures to the participants carefully both in the informed consent form and during the first training session to remind participants about the importance of following the entire intervention program. We will also send them a mid-intervention postcard reminder and will monitor closely the weekly questionnaire response rates, sending reminders to those who do not fill out the questionnaires by the deadlines indicated in the emails. We will further assess adherence to the intervention program with the process evaluation.

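### Session 2 returns need-satisfaction scores before participants rate their own dose, effort and goal attainment, an avoidable risk to the planned link between process and effect results

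*Protocol article*

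**What the plan says.** The Training sessions section of the protocol article sets the order of the second session. Participants come in and "they first fill out the last weekly questionnaire and will receive new individual needs satisfaction scores, which they can compare to their baseline scores". The step after that is described as follows: "Next, they have a chance to reflect on their experiences by identifying enablers and barriers that affected their off-job crafting during the intervention period". They then go over earlier goals, set new ones and may ask questions. Last, they are asked to "fill out a process evaluation questionnaire at the end of the training session to gather information about intervention reach, dose received" and attitudes to the programme.

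The Process evaluation section confirms the timing ("At the end of the second training session, a process evaluation will be conducted") and lists the content. "Participants are asked to indicate the extent that they participated in the intervention, the level of effort invested in following the intervention". For the app, "we ask participants to indicate how many Dailys they have completed and whether they also logged all the completed Dailys to the app". Goal attainment over the intervention period is self-rated from 0 to 100%.

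Under Strengths and limitations, the article names as its main limitation that a two-arm design cannot separate the intervention's components. It offers the process evaluation, which covers dose received among other things, as a partial answer. The stated aim is "to link the effect and process evaluation results to better understand the different mechanisms". The same section relies on the process evaluation to assess adherence.

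**The concern.** Dose received, effort and goal attainment are reported after participants have been given their own result on a hypothesised outcome. If that result influences the reports, part of any association between dose and need satisfaction runs from outcome to reported dose and not the other way. Someone shown a gain may recall more Dailys or rate goal attainment more generously, and someone shown no gain may do the reverse. Goal attainment is the most exposed item, because each participant's goal is built on one of the same six needs whose scores are returned.

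What is at stake is the reading of mechanism. The process data are the article's answer to its own main limitation, and an inflated association could be taken as evidence that doing more of the programme produced the gain. The order of data collection is fixed in the protocol, and later analysis cannot undo it.

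**Working it through.** **Order of events.** Set side by side, Training sessions and Process evaluation give this sequence within one session:

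1. Last weekly questionnaire, which contains the outcome items.
2. New need-satisfaction scores, for comparison with baseline.
3. Reflection on enablers and barriers.
4. Review of goals, new goals, questions.
5. Process questionnaire: participation, effort, Dailys, goal attainment.

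Step 2 precedes step 5, so the feedback can reach the dose items. Step 1 precedes step 2, so the feedback cannot reach the outcomes measured up to the end of the intervention.

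**Is the fed-back score an outcome?** Yes. The hypotheses at the end of the Background state that satisfaction of psychological needs will be higher during and after the intervention. The Measures section also lists it among potential moderators, mediators and control variables. It is the only construct the article says is returned at this session.

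**Is there a safeguard?** None is described. The article does not ask the dose items earlier, and it does not say that app records will serve as the dose measure.

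**Plan's own figure.** The plan gives no figure on this point. The only figure borrowed is 64 per group from Sample size calculation. Reading the stated effect size of .25 as f, which is d = 0.50 for two groups, with two-sided alpha .05 and power .80, the exact t-test gives 63.8, rounded up to 64. It reproduces, and serves only as the n below.

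**Illustration of sensitivity.** Let reported dose = true dose + λ × outcome change, both in standard-deviation units, with true correlation ρ. Then

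r = (ρ + λ) / √(1 + λ² + 2λρ)

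With ρ = 0 this is r = λ / √(1 + λ²), and the share of reported-dose variance due to feedback is r². The value of λ is an assumption; the documents give none. The rate of p < .05 was simulated with 4,000 runs at n = 64.

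| λ (assumed) | r when ρ = 0 | variance share r² | two-sided p < .05 |
|---|---|---|---|
| 0 | 0 | 0 | 4.8% |
| 0.1 | 0.1/√1.01 = 0.10 | 1% | 11% |
| 0.2 | 0.2/√1.04 = 0.20 | 4% | 34% |
| 0.3 | 0.3/√1.09 = 0.29 | 8% | 65% |
| 0.5 | 0.5/√1.25 = 0.45 | 20% | 96% |

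If a true relation exists, the same mechanism inflates it. With ρ = 0.20 and λ = 0.2, r = 0.40/√1.12 = 0.38.

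The table shows what would follow from a given amount of leakage. It is not evidence that leakage occurs.

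**The case against.** A reader might infer that the dose measure is contaminated and that a dose-response association will appear even if dose does nothing. The documents do not support that. They say only that participants can compare scores; nothing shows that doing so shifts their ratings. The magnitude calculation restates an assumed variance share as a correlation, and the assumed share may be very small. This objection stands, and the point is therefore put as a risk of unknown size.

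A reader might also infer that a specified analysis is compromised. Neither Effect evaluation nor Moderator and mediator analyses mentions dose, Dailys, effort or goal attainment. The link is a general aim in the discussion, and the process evaluation it draws on also covers recruitment, reach, fidelity, context, implementation and dose delivered. This too stands: no dose-response model is given, and one may exist in a document not shown. It does not answer the point about order, because a later model would use data already collected this way.

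Nor is the session feedback the only route. Participants know how they feel, and under Everydaily app they can follow graphs of need satisfaction and well-being throughout. The points they collect for completed Dailys may also aid recall. So reordering cannot remove the risk. But the session feedback is the one route the researchers schedule themselves, immediately before the dose items.

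Finally, a reader might extend the worry to outcomes in general, or to the trial's main comparison. Vitality, fatigue, stress, work engagement and performance scores are not described as returned to participants at this session. The randomised comparison up to the end of the intervention is untouched.

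**Conclusion.** The point holds as an avoidable risk. The session order lets feedback on one outcome, need satisfaction, colour self-reported dose, effort and goal attainment. If it does so in the direction of the scores shown, any association between dose and need satisfaction is inflated. Associations with other outcomes are exposed at most indirectly.

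The size cannot be derived from the documents and may be zero. Only under assumed leakage does it take a value, as tabulated above; that rests on a linear model, 64 intervention participants and leakage in the direction of the feedback.

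This is a modest point about an exploratory aim. It merits a change because that aim is the article's own response to its main limitation and the change is nearly free.

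**What to change.** In session 2, place the extent-of-participation, effort, Dailys and goal-attainment items straight after the outcome items of the last weekly questionnaire, and release the new scores only once these are submitted. Putting them after the outcome items keeps them from influencing the outcome answers. Leave satisfaction, trainer and open-text items at the end of the session, where they may properly reflect the whole programme.

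The cost is a change of item order within one session: no new items, visit or staff.

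An option is to add short past-week exposure items after the outcome items in each weekly questionnaire. This shortens recall from four weeks to one, at about a minute per week. The small downside is an extra prompt to self-monitor in the intervention arm only. The reordering within session 2 is enough without it.

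Under either version, dose and outcome are still self-reported in one sitting by people who sense their own progress and have seen the app graphs. Any dose association should therefore still be reported as observational, with that caveat.

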### Everydaily app

During the first training session, participants will be given individual access codes and instructions for using the Everydaily smartphone app. The app content is specifically developed to present participants with short daily activities (Dailys) to support engagement in off-job crafting behaviors. Participants will create a 4-week wellbeing project in the app. Each day, they are presented with three different Dailys, each addressing at least one of the psychological DRAMMA needs (i.e., detachment, relaxation, autonomy, mastery, meaning, affiliation). Participants are encouraged to select and complete Dailys that correspond to the psychological need that they have selected to focus on during the intervention period. Dailys are based on various techniques (e.g., mindfulness meditation, practicing gratitude, goal setting) that target different DRAMMA needs and have been previously shown to improve well-being [38–40]. After participants have completed a Daily, they can upload a picture or short reflection text about the task to the app. Participants’ picture and text submissions remain private and will only be visible to themselves. Additionally, they are asked to rate the level of DRAMMA needs fulfillment that they experienced during completing the Daily. Participants can additionally rate their well-being within the app. They can collect points for completing Dailys and can follow their progress in terms of needs satisfaction and well-being on graphs within the app. They are encouraged to use the gamified app throughout the intervention period.

### Measures

All seven questionnaires will include the following constructs: off-job crafting, subjective vitality, mental fatigue, stress, health status, private life satisfaction, job satisfaction, work engagement, family role performance, job performance, organizational citizenship behavior, basic need satisfaction, satisfaction of psychological needs, home demands, job demands and job crafting. Additionally, the baseline questionnaire will include need strengths, proactive personality, focus on opportunities, Selection, Optimization, and Compensation strategies and background variables. Both the baseline and the fourth weekly questionnaire will additionally measure participation in different off-job activities.

### Off-job crafting

Off-job crafting is measured with a new 18-item off-job crafting scale at the baseline and with a shortened 6-item version during and after the intervention period [24]. Crafting for each of the six DRAMMA needs is measured by three items at the baseline and one item during and after the intervention period. Example items are: “Over the past week, I’ve made sure to detach from work-related thoughts during off-job time” (detachment), “Over the past week, I’ve made sure to experience relaxation of my body and mind during off-job time” (relaxation), “Over the past week, I’ve planned my off-job activities so that I experience control over my life” (autonomy), “Over the past week, I’ve organized my off-job activities so that I put my skills, knowledge or abilities into action” (mastery), “Over the past week, I’ve made sure to experience meaning in my life during off-job time” (meaning), and “Over the past week, I’ve made sure to experience close connections to the people around me during off-job time” (affiliation). Participants are asked to respond on a 5-point Likert scale (1 = never, 5 = very often).

### Well-being

#### Subjective vitality

Subjective vitality is assessed with four items from the Subjective Vitality Scale [41, 42]. Participants are asked to indicate on a 5-point scale how often they felt alive and vital, energetic, having energy and sprit, and looked forward to each new day over the past week. The response scale ranges from 1 (very rarely or never) to 5 (very often or all the time).

#### Mental fatigue

Mental fatigue is measured with four items from the Three-Dimensional Work Fatigue Inventory [43] mental fatigue subscale. The items are adapted to one-week period. An example item is: “Over the past week, how often did you feel mentally worn out at the end of the workday?”. The response scale ranges from 1 (never or almost never) to 5 (very often or all the time).

#### Stress

Stress symptoms are measured with a one-item scale adapted from Elo, Leppänen and Jahkola [44]. First, participants indicate whether they have felt stress symptoms over the past week on a scale ranging from 1 (not at all) to 5 (very much). If applicable, participants are asked to specify in which life domain they experienced this kind of stress within the past week. They can indicate this on a scale from 1 (only during off-job time) to 7 (only at work) with the scale’s middle point indicating stress both in private and work life.

#### Health status

Health status is measured with one item [45]. Participants are asked to assess their current general health status on a scale from 1 (very bad) to 5 (very good).

#### Private life satisfaction

Private life satisfaction is measured with a single item adapted from job satisfaction item: “How satisfied have you been with your private life over the past week?”. In this context, private life refers to everything outside of work context, including family life, leisure activities, domestic chores, hobbies. Participants are asked to indicate their private life satisfaction on a scale ranging from 1 (very dissatisfied) to 10 (very satisfied).

#### Job satisfaction

Job satisfaction is measured with a single item: “How satisfied have you been with your job over the past week?”. A single-item measure has been shown to be acceptable to measure job satisfaction [46]. Participants can indicate their job satisfaction on a scale ranging from 1 (very dissatisfied) to 10 (very satisfied).

#### Work engagement

Participants work engagement is assessed with six items from the Utrecht Work Engagement Scale vigor and dedication subscales [47]. The items are adapted to one-week period. Example items are: “Over the past week at my work, I felt bursting with energy” (vigor) and “Over the past week, I was enthusiastic about my job” (dedication). Participants can choose between seven response options from 0 (never) to 6 (always).

### Performance

#### Family role performance

Participants’ performance in private life is assessed with a family role performance scale developed by Chen and colleagues [48]. The 4-item subscale measuring relationship performance in one’s family life is used in this study. The items are adapted to one-week period. An example of relationship performance item is: “Providing emotional support to your family members”. Participants can indicate to what extent their feel that they fulfilled what was expected of them in relation to different aspects of their current family life on a scale from 1 (did not fulfill expectations at all) to 5 (fulfilled expectations completely).

#### Job performance

To measure job performance, participants are asked to rate their overall work performance over the past week on a single-item measure [49]. The scale ranges from 1 (the worst job performance a person could have at your job) to 10 (performance of a top worker at your job).

#### Organizational citizenship behavior

Organizational citizenship behavior is measured with five items from a scale developed by Lee and Allen [50] and an additional item by Goodman and Svyantek [51]. The first three items measure behaviors directed towards the individuals. An example item is: “You have assisted others with their duties”. The next three items measure behaviors directed towards the organization, such as: “You offered ideas to improve the functioning of the organization”. Participants are asked how often they have engaged in these behaviors over the past week on a scale from 1 (never) to 7 (always).

### Potential moderators, mediators and control variables

#### Need strengths

Need strengths is measured with the baseline questionnaire. The items are adapted from Chen and colleagues [25]. In the current study, we use one question per dimensions for detachment and relaxation needs and two questions per dimension for autonomy, mastery, meaning, and affiliation needs. Example items are: “It is important to me to mentally disengage from my work during my off-job time” (detachment), “It is important to me to relax after my work is done” (relaxation), “It is important to me to feel in control” (autonomy), “It is important to me to develop my skills and abilities” (mastery), “It is important to me to achieve a sense of purpose in what I am doing” (meaning) and “It is important to me to experience close connections to the people around me” (affiliation). The need strength is measured on a scale from 1 (not important at all) to 5 (very important).

#### Basic need satisfaction

Basic need satisfaction is measured with nine items from the Basic Psychological Need Satisfaction and Frustration Scale [25]. The scale is reduced to three items per each psychological need based on the highest factor loadings in the study conducted by Chen and colleagues [25]. The items are adapted to one-week timeframe. Example items are: “Over the past week, I’ve felt a sense of choice and freedom in the things I undertook” (autonomy), “Over the past week, I’ve felt capable at what I did” (competence) and “Over the past week, I’ve felt that the people I care about also cared about me” (relatedness). Participants are asked to respond on a 5-point Likert scale (1 = completely untrue, 5 = completely true).

